**Methods:**

A 2-arm, single-blind randomized controlled trial will recruit 172 participants through Chinese hospitals and online platforms. Eligible participants will be randomized to 2 groups: a 10-week gamified pain management program for the experimental group and routine online pain management materials for the control group. Primary outcomes, including pain intensity and pain interference, and secondary outcomes, including fear avoidance, emotion, exercise adherence, quality of life, and user satisfaction, will be assessed at baseline, after the intervention (10 weeks), and at a 3-month follow-up. A mixed-design ANOVA and intention-to-treat analysis will be used to evaluate intervention effects.

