## Methods

### Study Design and Setting

This study is a 2-arm, single-blind (analysts are blinded), randomized controlled trial. A total of 172 individuals with chronic pain will be recruited and randomly assigned to either gamified pain management program (intervention group) or a digital resource package (control group). The interventions for both groups will be delivered online. Participants will complete outcome assessments at 3 time points: baseline (T0), immediately after the intervention (T1), and at a 3-month follow-up (T2). This study protocol follows the SPIRIT (Standard Protocol Items: Recommendations for Interventional Trials) guidelines [23].

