### Sample Size

A previous power analysis was used for sample size calculations using G*Power software (version 3.1; Heinrich-Heine-Universität Düsseldorf) [24]. To establish the effect size for the sample size calculation, we synthesized evidence from multiple sources. A meta-analysis analyzing the effects of serious games on pain intensity in patients with chronic pain reported a mean difference of −0.62 (95% CI −1.15 to −0.10) for pain reduction [18]. To supplement this, we conducted another meta-analysis of 12 relevant studies examining the effects of gamification on pain intensity in adults. The results yielded a mean difference of −0.86 (95% CI −1.61 to −0.11) [25-36]. However, given that our digital intervention comprises mixed physical, psychological, and educational components, we also incorporated evidence from 2 other meta-analyses including online pain management and multidisciplinary programs, with effect size of −0.30 (95% CI −0.50 to −0.10) [12] and −0.57 (95% CI −0.63 to −0.50) [37].

Therefore, to ensure robust and conservative statistical power, we selected a medium effect size of 0.50 to reduce potential bias or heterogeneity [38]. The following parameters were used: power (1−β)=0.90, effect size=0.50, and α=.05 (2 tailed). Taking a 20% margin for dropout and missing data, a total of 172 participants will be recruited, with 86 allocated to the experimental group and 86 to the control group.

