### Statistical Analysis

SPSS (version 25.0; IBM Inc) will be used for all statistical analyses. An intention-to-treat analysis will be used, whereby all participants will be analyzed in the context of the groups to which they had been originally assigned. Descriptive statistics for feasibility will include the following: (1) the percentage of participants recruited from the total number approached; (2) the percentage of participants (among those recruited) who are retained in the study at the end of 3 months in each arm and overall; and (3) engagement metrics, including completion status, duration of the intervention, and rate of accuracy on quizzes.

To detect potential differences in sociodemographic and baseline clinical characteristics, the *χ*^2^ test with continuity correction (or the 2-sided Fisher exact test when appropriate) will be used for categorical variables, and the *t* test will be used for continuous variables. The normality of distributions will be confirmed using the Shapiro-Wilk test before statistical analysis. Repeated measures ANOVA (mixed design: within and between groups) will be used to determine the overall effectiveness of the intervention. Missing values will be addressed using intention-to-treat principles with maximum likelihood estimation, assuming data are missing at random. Statistical significance will be set at *P*<.05.

The interviews will be transcribed verbatim and reviewed. Open and axial coding will be used for data identification and integration, resulting in different meaning categories derived using grounded theory methods. NVivo (QSR International Inc) will be used for the coding process and information handling.

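### The named effectiveness test, a mixed-design repeated measures ANOVA, does not deliver the all-participants, maximum-likelihood analysis promised in the same paragraph

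*Protocol article*

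**What the plan says.** The protocol article fixes four things in its Statistical Analysis section.

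- Software: "SPSS (version 25.0; IBM Inc) will be used for all statistical analyses". No SPSS procedure is named.
- Analysis set: under intention to treat, "all participants will be analyzed in the context of the groups to which they had been originally assigned".
- Effectiveness test: "Repeated measures ANOVA (mixed design: within and between groups) will be used to determine the overall effectiveness of the intervention". The abstract repeats this: "A mixed-design ANOVA and intention-to-treat analysis will be used to evaluate intervention effects".
- Missing data: "Missing values will be addressed using intention-to-treat principles with maximum likelihood estimation, assuming data are missing at random".

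The Study Design and Setting section gives three assessments: baseline (T0), end of intervention (T1) and 3-month follow-up (T2). The Sample Size section allows a 20% margin for dropout and missing data in a total of 172, 86 per arm. It uses "power (1−β)=0.90" with an effect size of 0.50 and a two-sided 5% level. The Anticipated Findings section hypothesises benefit on both primary outcomes at both T1 and T2.

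**The concern.** The parenthesis in the ANOVA sentence, together with the abstract's label, describes the split-plot design with one between-group and one within-person factor. In SPSS the classical form of that analysis is fitted by least squares to participants with complete data. It has no likelihood step for missing outcomes, and it needs a stronger assumption than missing at random. An analyst who follows the ANOVA sentence therefore breaks the analysis-set and missing-data sentences. One who follows those two sentences must fit a model that the article does not name.

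This is not detail left to an analysis plan. The article states both a test and a missing-data method, for both primary outcomes, and they do not fit together. Left as it is, the choice between them can be made after the data are seen. At stake are the valid T1 values of everyone who misses T2, the power that goes with them, and possibly some bias.

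**Working it through.** **1. The plan's own sample size.** Inputs from the Sample Size section: effect size 0.50, two-sided α 0.05, power 0.90. A two-sample t-test (noncentral t) needs 85.03 per arm, so 86 per arm and 2 × 86 = 172. The stated total is reproduced with no dropout added. With a 20% margin the same inputs give 86 / 0.80 = 107.5, so 108 per arm. That shortfall is a separate matter. It matters here because it leaves no reserve for deleted cases.

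**2. Participants lost to complete-case deletion.** If 20% lack at least one assessment, 0.20 × 172 = 34.4, or about 34, leave the ANOVA. About 138 remain (86 × 0.80 = 68.8, about 69 per arm).

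**3. Power on the plan's own basis** (two-sample t-test, effect size 0.50, two-sided α 0.05):

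| Loss | Per arm | Power |
|---|---|---|
| 0% | 86 | 90.3% |
| 10% | 77.4 | 87.1% |
| 20% | 69 | 83.0% |
| 30% | 60.2 | 77.7% |

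**4. Possible bias (illustration only).** The article gives neither visit correlations nor a dropout mechanism, so the following are assumptions: correlations T0–T1 0.5, T1–T2 0.7, T0–T2 0.4; true effect −0.50 SD at T1 and T2; 20% of each arm lost before T2; log-odds of dropout changing by 0.5 per SD of T1 pain. The group-by-time test works on change from baseline, so the contrast in completers is (intervention − control at the visit) − (intervention − control at T0).

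| Dropout depends on T1 pain | Change contrast T1 | Change contrast T2 |
|---|---|---|
| In the control arm only | about −0.45 | −0.48 |
| In opposite directions by arm | −0.41 | −0.47 |
| Equally in both arms | −0.50 | −0.50 |

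Repeat runs differ by about 0.01. A likelihood-type estimate of the T2 difference, which regresses T2 on T0 and T1 within arm and averages over everyone in the arm, stays at −0.50 in all three cases. The direction of bias also depends on the assumptions. With all correlations 0.5, about 17.5% loss and a slope of 1 per SD (higher pain raising dropout in the intervention arm and lowering it in the control arm), the raw completer difference at T2 was −0.65 against a true −0.50.

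**The case against.** The best defence is that the article names no SPSS procedure, and the phrase mixed-design ANOVA is often used loosely. SPSS can fit a group-by-time repeated measures model by maximum likelihood in MIXED. Read with the missing-data sentence, the ANOVA sentence could mean exactly that, and a complete-case analysis is what the text says it will not do. Part of this stands: the software is no obstacle, and the authors may intend the right model. But both places that name the test name an ANOVA, nothing links it to a likelihood fit, and the article should not depend on a charitable reading for its primary analysis.

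Three stronger readings are tempting, and the documents do not support them.

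- *That the promised analysis cannot be done as planned.* The mismatch lies in the test named, not in what SPSS can do.
- *That the result will be badly biased.* Raw completer differences at T1 of about −0.41 and −0.32 against −0.50 can be produced under arm-specific dropout, but the group-by-time test uses change from baseline, where the distortion is smaller. The Introduction attributes low retention to existing online programmes. For this trial the article gives only the 20% margin, and both arms receive biweekly reminders. Nothing says that dropout will depend on pain differently by arm.
- *That the type I error will be inflated.* Filling in values once and then running the ANOVA gave 7–11% instead of 5% in simulation under assumed correlations. The article does not mention such a step, so this only illustrates one way an analyst might try to reconcile the sentences.

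**Conclusion.** The mismatch is real and concerns the primary analysis: the named ANOVA, in its classical SPSS form, does not give the promised analysis of all participants under missing at random. The firm consequence is lost data and power. At 20% loss about 34 of 172 participants are dropped, and power at an effect size of 0.50 is about 83% rather than 90%. This rests on the plan's own t-test basis and on the 20% being spread equally over the arms.

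Bias is conditional. On the stated assumptions, dropout that depends on pain differently by arm moves a true −0.50 to about −0.41 to −0.48 on the change contrasts. Equal dependence and equal loss cost only power. A likelihood model would not restore the full 90%, since a missing outcome still carries less information than an observed one. It would keep every observed T1 and T2 value and match the stated missing-at-random assumption.

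**What to change.** In the Statistical Analysis section and the abstract, replace the repeated measures ANOVA with a likelihood-based linear mixed model for repeated measures (SPSS MIXED) with group, visit and group-by-visit terms. State that it uses every available value from all randomised participants, in the group assigned. For both primary outcomes, report the group difference with a 95% CI at T1 and at T2, which matches the hypothesis of benefit at both times. The covariance structure, the choice between ML and REML and the form of baseline handling can be left to the analysis plan. Any bias or type I error figures quoted in support should be labelled as illustrations that depend on assumed correlations and dropout.

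The cost is a few sentences, with the same software and the same data collection. The Study Timeline section reports 19 participants recruited by 17 November 2025 and no analysis begun, so the change can be made before any outcome data are analysed.

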### Procedure and Randomization

The eligibility screening survey will automatically classify individuals after clicking the Agree button as they agree to provide consent. Screening questions will consist of pain intensity, pain duration, health history, recent treatment enrollment, and demographic data. The survey will be designed with conditional logic such that individuals who do not meet the eligibility criteria will be automatically redirected to the end of the survey and prompted to submit their responses. This approach means individuals who are not eligible will neither complete the full survey nor engage in the intervention. Conversely, eligible individuals will proceed to complete the remaining sections, which constitute the full baseline assessment. At the end of the questionnaire, interested participants may provide their WeChat account to receive group allocation and intervention information.

Following baseline assessment, enrolled participants will be randomly assigned in a 1:1 ratio to either the intervention or the control group. A computer-generated randomization sequence using blocks of sizes 2 and 4, stratified by age and sex, will be used. The randomization process will be managed by an independent researcher (JH), and allocation numbers will be stored securely in a password-protected database. Allocation will be revealed to the intervention deliverer ([name], a PhD student) only after a participant is enrolled. The intervention deliverer will be blinded to data assessment and data analysis.

After randomization, participants will be notified of their group allocation and provided with preassigned WeChat log-in credentials. Those in the intervention group will receive a direct message containing a hyperlink to access the gamified pain management platform, while those in the control group will receive a digital resource package. After the intervention, T1 (10 weeks immediately after intervention) and T2 (3-month follow-up) assessments will be collected via the Wenjuanxing platform [39], and semistructured interviews will be conducted to collect individual’s perceptions and experiences of the intervention. Participants who report the most, moderate, or least change in pain intensity will be invited to participate in the interviews.

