#### Primary Outcome

Pain intensity and pain interference are assessed using the Brief Pain Inventory between baseline, T1, and T2, rated from 0 (no pain) to 10 (worst pain). Pain severity is calculated based on pain experienced in the past 24 hours and “current pain.” Pain interference includes the degree to which pain interferes with general activity, mood, walking, work, social relationships, sleep, and enjoyment of life. The Chinese version has good reliability, with Cronbach α=0.89 [51].

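### The mixed ANOVA named for effectiveness is valid, but it is not aligned with the hypothesised T1 and T2 differences and names no adjustment for baseline or the randomisation strata

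*Protocol article*

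**What the plan says.** Statistical Analysis names one model for effectiveness: "Repeated measures ANOVA (mixed design: within and between groups) will be used to determine the overall effectiveness of the intervention". The Abstract repeats the choice. Neither place lists a covariate, a contrast, or the ANOVA term that decides the result. Missing values are to be handled by maximum likelihood under missing at random.

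Primary Outcome describes the measurements: "Pain intensity and pain interference are assessed using the Brief Pain Inventory between baseline, T1, and T2". Baseline is therefore most naturally read as a level of the within-subject factor.

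Procedure and Randomization says: "A computer-generated randomization sequence using blocks of sizes 2 and 4, stratified by age and sex, will be used". Anticipated Findings hypothesises lower pain intensity and interference than control at the end of treatment and again at 3 months, and expects age and sex to be related to recovery.

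Sample Size gives the design inputs: "The following parameters were used: power (1−β)=0.90, effect size=0.50, and α=.05 (2 tailed"). It then states: "Taking a 20% margin for dropout and missing data, a total of 172 participants will be recruited". This total is split equally, giving two arms of 86.

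**The concern.** The hypothesis is about two between-group differences, one at T1 and one at T2. A mixed ANOVA over T0, T1 and T2 offers two candidate tests, and neither is that pair.

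- **Group main effect.** This is the literal reading of *overall*. It averages in T0, where randomisation makes the expected difference zero, and so dilutes the effect.
- **Group-by-time interaction.** This is a 2-df omnibus test of differential change. It gives no estimate at T1 or T2.

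Baseline scores and the age and sex strata are in hand and would sharpen the comparison, but the named model makes no stated use of the strata and uses baseline only as a response. At stake are precision and power, and a choice between ANOVA terms that is left open until data are seen.

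**Working it through.** **Inputs from the article:** two-sided α = 0.05, power 0.90, effect 0.50 SD, 86 per arm, 20% loss.

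**Assumptions, not in the article:** SD of 1 at every visit; the same correlation r between any two visits, taken as 0.3, 0.5 and 0.7; true effect 0 at T0 and 0.50 SD at T1 and T2; for group-by-time, also a variant in which the effect halves to 0.25 SD at T2.

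**Step 1: the article's own figure.** An exact two-group t test at d = 0.50 needs 86 per arm (172 in total) for 90% power; power at 86 is 90.3%. So 172 is the sample size for an unadjusted comparison at one visit before any loss. After 20% loss, 172 × 0.8 = 137.6, or about 69 per arm, and the same t test has 83%. (The missing dropout allowance is a separate issue; it matters here only because it removes spare power.)

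**Step 2: group main effect.** The difference averaged over visits is (0 + 0.50 + 0.50)/3 = 0.33. The SD of a participant's three-visit mean is √((1+2r)/3) = 0.730, 0.816, 0.894. The standardised effect is 0.456, 0.408, 0.373.

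**Step 3: group-by-time.** The visit effects (0, 0.50, 0.50) deviate from their mean by (−1/3, 1/6, 1/6), with sum of squares 1/6. The noncentrality is λ = (n/2) × (1/6)/(1−r) = 34.5/6/(1−r) = 5.75/(1−r) = 8.2, 11.5, 19.2, on 2 and 2 × (138−2) = 272 df. If the effect halves by T2, the deviations are (−0.25, 0.25, 0), with sum of squares 0.125, and λ = 4.31/(1−r) = 6.2, 8.6, 14.4.

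**Step 4: baseline-adjusted contrast at one visit.** The effect is 0.50/√(1−r²) = 0.524, 0.577, 0.700.

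**Power at 69 per arm**

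| Test | r = 0.3 | r = 0.5 | r = 0.7 |
|---|---|---|---|
| Group main effect, T0 to T2 | 76% | 66% | 58% |
| Group-by-time, effect sustained | 72% | 86% | 98% |
| Group-by-time, effect halved by T2 | 59% | 75% | 93% |
| Unadjusted t test, one visit | 83% | 83% | 83% |
| Baseline-adjusted, one visit | 86% | 92% | 98% |

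The last two rows apply to a visit where the true effect is 0.50 SD. The adjusted contrast needs 78, 65 and 44 evaluable per arm for 90% power. With no loss at all (86 per arm), the main effect has 85%, 76%, 68%; group-by-time with a sustained effect 82%, 93%, 99.5%; the adjusted contrast 93%, 96%, 99.5%.

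**Step 5: omitting the strata.** If age and sex explain a share R² of outcome variance and are balanced by design, the unadjusted standard error at one visit is too large by the factor 1/√(1−R²). For an assumed R² of 3% to 10% this is 1.015 to 1.054. For the three-visit main effect, a stratum effect that is constant over time is a larger share of the variance of the mean: R²/((1+2r)/3), or 1.5 × R² at r = 0.5. The factor is then 1/√(1−0.045) = 1.02 to 1/√(1−0.15) = 1.08. A null simulation (10,000 runs, 86 per arm, r = 0.5) with R² = 5%, 10%, 20% gave type I error 0.041, 0.032, 0.021 for the main effect and 0.051, 0.053, 0.050 for group-by-time. The error is conservative for the first and absent for the second.

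**The case against.** The strongest reply is that one sentence in a condensed article names a model family, not a full specification. Covariates and contrasts may sit in an analysis plan that is not shown, and the article nowhere says they are excluded. That stands, so it cannot be claimed that the trial will refuse to adjust. What the article does publish as its effectiveness analysis still leaves the deciding term open and does not match its own hypothesis.

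A reader might infer that the planned analysis gives wrong error bars. The documents do not support that. Leaving out the strata can only make the main-effect standard error somewhat too large, and it leaves group-by-time at its nominal level when stratum effects are constant over time.

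A reader might also infer that treating baseline as a response is an error. It is not: group-by-time is then a valid test of differential change, and under maximum likelihood this layout keeps participants who have only baseline data.

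The power comparison also has limits. The 66% at r = 0.5 applies only if the main effect is the test. Group-by-time at r = 0.5 has 86%, above the unadjusted t test, and at r = 0.7 it equals the adjusted contrast. The adjusted figure concerns one visit while the omnibus test covers both, so the two answer different questions. The 69 per arm counts completers only, whereas likelihood estimation would recover some information from partial data.

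**Conclusion.** The point holds as one of efficiency and alignment, not validity. Under the stated assumptions the baseline-adjusted contrast is at least as powerful as either ANOVA term at every correlation tried. At 69 per arm it has 86% to 98%, against 58% to 76% for the main effect and 72% to 98% for group-by-time (59% to 93% if the effect halves by T2). The gain over group-by-time with a sustained effect is 14 points at r = 0.3, 6 at r = 0.5, and none near r = 0.7. Ignoring the strata costs about 1.5% to 5% in the single-visit standard error if they explain 3% to 10% of variance. The correlation, that share, and the equal-correlation structure are assumptions; the article gives none of them.

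It might also be tempting to conclude that T1 should be the primary contrast with T2 behind it. The article's hypothesis names both time points and does not rank them, so that ordering is not supported.

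**What to change.** State as the primary analysis, for each primary scale, a likelihood-based mixed model with T1 and T2 as outcomes. Its fixed effects are group, time, group-by-time, the baseline value of the same scale, baseline-by-time, age stratum and sex. Report the adjusted group difference with its confidence interval at T1 and at T2, since both are hypothesised. Use the same form for every secondary scale measured at T0 in both arms. This fits the existing commitment to maximum likelihood under missing at random.

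The cost is small: a change of wording and slightly more modelling, with baseline, age and sex already collected. According to Study Timeline, 19 participants had been recruited by 17 November 2025 and analysis had not begun, so the change can be dated before any results are seen. The one downside is that participants with only baseline data no longer contribute. If that matters, keep baseline as a response and constrain the baseline means to be equal between arms.
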